### Randomization

2.5

This study is a randomized, double-blind, sham-controlled trial, where participants will be randomly assigned to either the intervention group or the control group. The random allocation of participants will help prevent selection bias and ensure a balanced distribution of confounding factors between the study groups. For the randomization process, blocked randomization will be employed. Specifically, one of the six blocks used in this study (ABAB, BABA, AABB, BBAA, BAAB, ABBA) will be randomly selected. A will represent the intervention group, and B will represent the control group. Each participant will be assigned an ID number and allocated to one of the treatment groups. The individual who generates the random allocation will not be involved in any other phase of the trial.

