#### Speech therapy (pre-practice or establishment stage)

2.3.1

Both the control and intervention groups will undergo this treatment stage before the start of the tDCS intervention, which will be referred to as the pre-practice(establishment stage). In this stage, the clinician will work with the participant to practice fluency shaping techniques, progressing from simple to complex levels. Each participant will engage in 1–2 h intensive sessions at the clinic to practice fluency-shaping techniques (such as easy onset, airflow, pausing, light consonant contact, and prolongation) at basic levels (phonemes, syllables, words, sentences, and phrases) with the clinician. Subsequently, more complex tasks will be introduced, including reading, monologues, dialogues with the clinician, dialogues and monologues in the presence of strangers, and practicing telephone calls. The goal of this stage will be to ensure that the participant can use fluency shaping techniques in various speech tasks with the clinician in the clinic before entering the combined intervention stage (fluency shaping techniques and brain stimulation). The study participants will be expected to maintain a severity rating (SR) below 2 during these tasks before proceeding to the practice stage. This stage will ensure that clients can use the restructured speech techniques at a simple level with the clinician at the clinic. Then, clients will use these techniques during more complex online practice tasks along with anodal tDCS/Sham tDCS.

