### Blinding

2.6

As the study is double-blind, neither the participants nor the researcher will know of the group assignment for each participant. Sealed, opaque envelopes will be used to ensure concealment. A separate envelope will be created for each participant, labeled with an ID number, and the corresponding treatment group for each ID will be placed in its designated envelope. To ensure double blinding, the actual names of the treatment groups (intervention and control) will be replaced with specific codes unknown to both the principal investigator and the participants. A clinician, independent of the principal investigator, will assign these codes to the corresponding treatment groups. Before the principal investigator begins treating a participant, the clinician will provide the participant with one of the sealed envelopes. After the participant opens the envelope, the clinician will configure the mode—either anodal or sham—according to the envelope's contents and attach the electrodes to the participant's head as described in the above sections. After the setup is completed, the principal investigator will initiate the treatment. Additionally, the researchers conducting the outcome assessments and data analysis will remain blinded to the group assignments.

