### Sample size

2.9

Based on the previous investigations conducted by Karsan et al. and Moien et al. [25,26], and employing G∗Power software [47], it is determined that 31 subjects per group (totaling 62 participants overall) are required to detect a statistically significant difference regarding a time × group interaction via a two-way mixed model analysis of variance (ANOVA). The time variable is designated as the within-subject factor (i.e., before the intervention and immediately, six weeks, and 3 months following the intervention), while the group is classified as the between-subject factor (i.e., anodal or sham tDCS). The dependent variable examined is the percentage of stuttered syllables (SS%). Type I (α) and type II (β) error rates are set at 0.05 and 0.20, respectively, with an effect size of 0.17.

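### Fixed, published blocks of four let the clinician who sets the stimulation mode deduce about a third of allocations in advance, if envelopes are used in sequence

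*Protocol article*

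**What the plan says.** Section 2.5 describes blocked randomization in which "one of the six blocks used in this study (ABAB, BABA, AABB, BBAA, BAAB, ABBA) will be randomly selected". It gives the key as well: "A will represent the intervention group, and B will represent the control group". It mentions no variation in block size and no stratification. The person who generates the list has no other part in the trial.

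Section 2.6 relies on sealed opaque envelopes labelled by participant ID, with codes in place of the group names. One clinician, separate from the principal investigator, has three tasks:

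- holding the key: "A clinician, independent of the principal investigator, will assign these codes to the corresponding treatment groups";
- handing over the envelope: "the clinician will provide the participant with one of the sealed envelopes";
- setting the device: "After the participant opens the envelope, the clinician will configure the mode".

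The principal investigator, participants, outcome assessors and analysts are to be blinded.

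Section 2.3.2 places random allocation in Stage 2. Before that, section 2.3.1 requires a severity rating (SR) below 2 on the practice tasks. It describes the aim thus: "The goal of this stage will be to ensure that the participant can use fluency shaping techniques in various speech tasks with the clinician". It does not say who gives the rating, or whether the Stage 1 clinician is the person who later sets the mode.

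**The concern.** Opaque envelopes stop anyone reading an assignment before it is opened. They do not stop anyone inferring it from earlier assignments when the block size is fixed and known. The mode-setting clinician necessarily learns each assignment and can keep a running count within the block.

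This matters more than usual because entry to the allocated stage is not automatic. It depends on a perceptual score (section 2.4.2.1). If someone who knows the next arm can affect whether or when a participant is judged ready, participants who responded well or badly to Stage 1 could collect in one arm.

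The planned analysis would not reveal this. Baseline %SS is measured before speech therapy starts (section 2.1), and no outcome assessment is scheduled between Stage 1 and allocation. A difference between arms in Stage 1 response would not show in baseline %SS. The group-by-time ANOVA of section 2.10 could not separate it from an effect of stimulation.

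**Working it through.** The article gives no figure for predictability, so there is none to reproduce.

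**Inputs**

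- Six blocks of four, each with two A and two B (section 2.5).
- 62 allocations, from "31 subjects per group (totaling 62 participants overall) are required" (section 2.9), used here only as a count: 62 = 15 × 4 + 2.
- Assumptions: a new block is drawn with probability 1/6 each for every four participants, there is one unstratified sequence, and envelopes are used in order at entry to Stage 2.

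**Certain allocations.** A place is certain once two of one arm have been used in the block. The best guess is the arm used less so far, or a coin toss when the arms are level.

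| Block | 3rd place certain | 4th place certain | Number certain | Expected correct guesses |
|---|---|---|---|---|
| ABAB | no | yes | 1 | 3.0 |
| BABA | no | yes | 1 | 3.0 |
| BAAB | no | yes | 1 | 3.0 |
| ABBA | no | yes | 1 | 3.0 |
| AABB | yes | yes | 2 | 2.5 |
| BBAA | yes | yes | 2 | 2.5 |

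- Certain per block: (4 × 1 + 2 × 2)/6 = 4/3 of 4, or 33.3%.
- Certain over the trial: 15 × 4/3 = 20. The last two places open a new block and add none. 20/62 = 32.3%. The variance per block is 2/9, so the SD is √(15 × 2/9) = 1.8.

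**Best guess**

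- Per block: (4 × 3.0 + 2 × 2.5)/6 = 2.833 of 4, or 70.8%.
- Over the trial: 15 × 2.833 + 1/2 + 2/3 = 43.7 of 62, or 70.4%.

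**A more literal reading of section 2.5.** If one block were drawn once and then repeated throughout, everything after the first block would be known: 58 + 4/3 = 59.3 of 62 (95.7%). The calculation above takes the more favourable reading.

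**Alternatives over 62 allocations.** The mixed schemes were simulated for an observer who knows the possible sizes but not their order.

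| Scheme | Certain | Best guess right |
|---|---|---|
| Fixed 4 | 32.3% | about 70% |
| Fixed 6 | 24.2% | about 68% (complete blocks) |
| Fixed 8 | 18.3% | about 67% (complete blocks) |
| Mixed 2/4/6 | 4.0% | 70.1% |
| Mixed 4/6 | 5.5% | 69.1% |
| Mixed 4/6/8 | 2.3% | 67.8% |

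Varying the size removes most of the certainty but hardly changes the best-guess rate. A complete fix must also separate knowledge of past allocations from the decision on entry.

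**The case against.** The strongest reply is that knowledge and influence may never meet in one person. Section 2.6 makes the mode-setter independent of the principal investigator, who treats the participant and is blinded. The word clinician appears in both 2.3.1 and 2.6, and a reader might infer that the same person runs Stage 1, rates SR and sets the mode. The article does not say so. If the blinded principal investigator judges readiness, the published block list is of no use for steering, because that person has no past allocations to count from. This stands: steering is a possibility that the text leaves open.

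Second, envelopes are labelled by ID. If IDs are fixed at enrolment, changing the order or timing of entry changes nobody's arm, and only keeping a participant out of Stage 2 altogether could distort the comparison. Participants could also finish Stage 1 out of ID order, and the share known at any moment would then differ from one third. This stands as a limit on the figure. It does not settle the matter, because section 2.6 speaks only of one of the envelopes and section 2.3.2 places allocation in Stage 2.

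Third, the list generator has no other role, and raters and analysts are blinded. These protect the generation of the list and the measurement of the outcome. They do not prevent prediction of the next assignment by the one unblinded person.

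**Conclusion.** The point holds in limited form. The fixed block size, the printed list and one clinician's knowledge of every past assignment all follow from sections 2.5 and 2.6. Given sequential use of envelopes and a new block for every four participants, that clinician can know about 20 of 62 allocations (32%) with certainty before the next participant enters Stage 2, and can guess about 71% correctly within complete blocks.

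A reader might infer that concealment fails, or that upcoming allocations are open to the whole team. The documents support neither. The foreknowledge belongs to one person (or anyone that person tells), and no passage gives that person control over entry. What can be said is that concealment can be compromised if the mode-setter has any influence on the readiness decision, and that the article does not rule this out. No amount of bias can be calculated from what is stated. The change is worth making because it is cheap and better than the stated method.

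**What to change.** 1. In section 2.5, replace the fixed blocks with block sizes that vary at random, known only to the independent list generator and not disclosed to site staff. If enrolment has begun, apply this to the remaining allocations. The old list is already in print, so removing it from site documents would not be enough. A new list is needed.
2. In sections 2.3.1 and 2.6, state that Stage 1 readiness is recorded by the blinded principal investigator, or by another person who does not set the mode, before that participant's envelope is handed over.
3. In section 2.6, state when IDs are assigned and that envelopes are used in sequence.

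The cost is a new list and a few sentences, with no extra staff. The downside is a possible end imbalance of a few participants. It cannot exceed half the largest block size, for example three with blocks of up to six. If the principal investigator already judges readiness, the second change only records current practice.

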### Blinding

2.6

As the study is double-blind, neither the participants nor the researcher will know of the group assignment for each participant. Sealed, opaque envelopes will be used to ensure concealment. A separate envelope will be created for each participant, labeled with an ID number, and the corresponding treatment group for each ID will be placed in its designated envelope. To ensure double blinding, the actual names of the treatment groups (intervention and control) will be replaced with specific codes unknown to both the principal investigator and the participants. A clinician, independent of the principal investigator, will assign these codes to the corresponding treatment groups. Before the principal investigator begins treating a participant, the clinician will provide the participant with one of the sealed envelopes. After the participant opens the envelope, the clinician will configure the mode—either anodal or sham—according to the envelope's contents and attach the electrodes to the participant's head as described in the above sections. After the setup is completed, the principal investigator will initiate the treatment. Additionally, the researchers conducting the outcome assessments and data analysis will remain blinded to the group assignments.

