#### Transcranial current direct stimulation Intervention(Practice stage)

2.3.2

In this stage of treatment, participants will be randomly allocated to two groups: the intervention group (anodal tDCS) and the control group (sham tDCS). Clients will practice fluency shaping techniques as an online treatment alongside each of ten 20-min tDCS stimulations. Clients will start by reading simple sentences and monologues during the first tDCS session but will eventually progress to more challenging tasks, such as conversing with the clinician, a stranger at the clinic, making telephone calls, and performing dual tasks. The tasks will become hierarchically more complex linguistically and cognitively.

In the tDCS protocol, electrical stimulation will be administered by applying a 2 mA current through two electrodes measuring 5 cm × 7 cm. The process will last for 40 min, with 15-s ramp-up and ramp-down intervals. Each therapy session will last 60 min (20 min of stimulation, 20 min of rest, followed by another 20 min of stimulation). Accordingly, each participant will receive 10 stimulation sessions over 5 therapy sessions conducted on 5 consecutive days. The tDCS will be administered using a Starstim DC stimulator. The tDCS electrodes will consist of conductive rubber encased in sponge pockets, with saline solution used as the electrolyte-based contact medium. It will be essential to saturate the sponges thoroughly with saline. The sponges will need to be properly moistened on all sides without becoming excessively saturated to avoid any dripping. Before placing the electrodes on the scalp, the clinician will examine the skin for any damage or lesions. The same stimulation intensity parameters will be applied for both anodal and sham modes. However, in the sham mode, the device will automatically reduce the intensity after 30 s. An electroencephalogram (EEG) cap will be utilized to determine the stimulation site. The anode electrode will be positioned over the left frontal gyrus (FC5, based on the 10–20 international system) [41], while the cathode electrode will be placed over the right frontopolar region (FP2, according to the same system) [41]. Elastic rubber straps will be used to secure the electrodes in place and prevent any movement.

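### The blinded participant opens the coded allocation envelope, and the article does not separate the unblinded clinician who sets the mode from the clinician who takes part in the speech therapy

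*Protocol article*

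**What the plan says.** **Who is blind.** Section 2.6 states that "neither the participants nor the researcher will know of the group assignment for each participant". It adds that outcome assessors and data analysts stay blinded.

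**The envelope.** Section 2.6 says that "the corresponding treatment group for each ID will be placed in its designated envelope". It then says that the group names "will be replaced with specific codes unknown to both the principal investigator and the participants". The participant receives the sealed envelope from the clinician, and the next step is: "After the participant opens the envelope, the clinician will configure the mode".

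**The operator.** "A clinician, independent of the principal investigator, will assign these codes to the corresponding treatment groups". The clinician also sets anodal or sham and attaches the electrodes. The principal investigator then starts the treatment.

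**The therapy partner.** Section 2.3.1 has the clinician train the participant in the fluency techniques. Section 2.3.2 lists the harder tasks done during stimulation, "such as conversing with the clinician, a stranger at the clinic, making telephone calls, and performing dual tasks", and also has the clinician inspect the skin before the electrodes go on.

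**The list.** Section 2.5 uses permuted blocks of four, described as "one of the six blocks used in this study", and explains that "A will represent the intervention group, and B will represent the control group".

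**The concern.** The sham arm isolates the effect of stimulation only if participants, and those who work with them during practice, do not know the arm. Two features of the stated procedure put this at avoidable risk.

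First, the participant handles and sees an allocation label. An uninformative label does no harm, but it does no good either. If the label is common to an arm, its meaning can be worked out once and then applied to others.

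Second, someone must know the mode in order to set it. That is unavoidable and not a flaw in itself. The risk arises if the same person is also a conversation partner during the stimulated tasks. Encouragement, task pacing or an unguarded remark could then differ by arm and change how the participant practises. That is performance bias, and it would carry through to later speech on the assessment calls. Blinded scoring of recordings cannot remove it. The OASES is completed by the participants themselves (Section 2.4.2.3), so a participant who learns or suspects the arm is not protected by blinded raters at all.

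**Working it through.** The main point is a comparison of sections; only the optional remark on block size needs arithmetic.

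**1. What the participant sees.** Section 2.6 first says the group goes into the envelope and then that the group names are replaced by codes. Read together, the envelope holds a code. What is coded is the name of each of the two groups, so the natural reading is two codes, one per arm, rather than one per participant. The article does not say so outright. It also does not say whether the letters A and B, whose meaning Section 2.5 states openly, are the envelope codes. If they were, the masking would fail; nothing in the text says that they are.

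**2. Who knows the arm.** The clinician of Section 2.6 assigns the codes to the groups and sets the device, and so is unblinded by function. The list of blinded people in 2.6 (participants, the researcher, outcome assessors, analysts) does not include this clinician.

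**3. Who delivers the therapy.**

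| Task | Section | Person named |
|---|---|---|
| Technique training, Stage 1 | 2.3.1 | the clinician |
| Skin check before electrode placement | 2.3.2 | the clinician |
| Conversation during stimulation | 2.3.2 | the clinician |
| Assigning codes | 2.6 | a clinician independent of the principal investigator |
| Setting the mode, attaching electrodes | 2.6 | the clinician |
| Starting the treatment | 2.6 | the principal investigator |

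Two readings fit. If the clinician of 2.3 is the blinded principal investigator, the blind holds as described. If that clinician is the operator of 2.6, an unblinded person takes part in the therapy. The skin check makes the second reading plausible, because it belongs to electrode placement, which 2.6 gives to the operator. The text does not decide between them.

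**4. Block size (optional point).** Section 2.5 lists six blocks: ABAB, BABA, AABB, BBAA, BAAB, ABBA. They hold 6 × 4 = 24 positions. A position is determined when the earlier letters of its block leave only one possibility.

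- Four blocks (ABAB, BABA, BAAB, ABBA) have a balanced first pair, so only the fourth letter is determined: 4 × 1 = 4.
- Two blocks (AABB, BBAA) have an unbalanced first pair, so the third and fourth are determined: 2 × 2 = 4.
- Total: (4 + 4)/24 = 8/24 = 33%.

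The chance of a correct best guess at positions 1 to 4 is:

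- position 1: 1/2;
- position 2: 2/3;
- position 3: (4/6)(1/2) + (2/6)(1) = 2/3;
- position 4: 1.

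The mean is (1/2 + 2/3 + 2/3 + 1)/4 = 17/24 = 71%, against 50% with unpredictable allocation. Both figures apply only to someone who knows the earlier allocations and where each block begins. The one role in 2.6 with knowledge of earlier allocations is the operator. This matters for selection only if that person also influences who passes from Stage 1 to Stage 2. That step depends on a severity rating below 2 (2.3.1), and the article does not say who gives the rating.

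**The case against.** The strongest reply is that the blind is already protected. The codes are expressly unknown to participants and to the principal investigator. The operator is introduced as a separate person, and the principal investigator treats. The raters of the primary outcome are blinded to condition and time point, and they work from coded recordings of calls made by people other than the researcher (2.4.1). Outcome assessors and analysts are blinded too. On the allocation side, envelopes are sealed and opaque, and the person who generates the list has no other role.

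Most of this stands. It rules out two stronger conclusions that a reader might draw:

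- *That opening the envelope unblinds the participant.* The text describes a code whose meaning the participant does not know. Decoding would need a further leak that the article nowhere describes.
- *That the unblinded operator is the therapy partner.* The evidence is a shared job title and the skin check, which make overlap possible but do not establish it.

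A reader might also take the wording of Section 2.5 to mean that one block is drawn and reused throughout. That is a strained reading of condensed text. Blocked randomization with six listed blocks fits a fresh draw for each block.

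The reply does not give a reason for the participant to see the code, or say which clinician converses with the participant during stimulation. The outcome safeguards address detection bias in the percentage of stuttered syllables; they do not address performance bias or the self-reported OASES.

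**Conclusion.** The procedure in Section 2.6 is weaker than it needs to be, and its roles are not reconciled with Sections 2.3.1 and 2.3.2. The article shows a possible route to unblinding, not a breach. The size of any resulting bias cannot be calculated from the article.

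The conclusion rests on two readings: that the codes are one per arm, which is natural but not explicit, and that the clinician of 2.3 may be the operator of 2.6, which is left open. If the sponsor can state that the codes are unique to each participant and that the operator takes no part in the speech tasks, little remains beyond the needless step of having the participant open the envelope.

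The block-size remark is secondary. The 33% is correct, but it depends on knowledge of earlier allocations and matters only if the person who has it can influence entry to Stage 2. The change is worth making because it costs little and protects the comparison on which the trial depends.

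**What to change.** **Section 2.6.** State that the independent clinician alone opens the envelope, out of sight of the participant and the principal investigator. Use a unique code for each participant in place of a code per group. State that this clinician takes no part in the Stage 2 speech tasks.

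**Sections 2.3.1 and 2.3.2.** Name the role that trains and converses with participants, using a title distinct from that of the operator, and make it agree with 2.6.

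**Section 2.5 (optional).** State that each block is drawn independently, and vary the block size at random, for example 2, 4 and 6, without disclosing the sequence to those who treat or enrol.

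**Cost.** A few sentences of procedure, a new allocation list, and a restriction on the duties of the independent clinician, a role that already exists. If that person currently serves as a conversation partner, a blinded member of the team would have to take over those tasks.
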